**10.2 Statistical analysis methods**

Categorical data is summarized descriptively using the statistics including frequency (n) and percentage (%), and the 95% confidence interval (CI) of the overall percentage is given. Continuous data is summarized descriptively using statistics including mean, standard deviation (SD), median, minimum and maximum. For time-to-event data, Kaplan-Meier method is used to estimate the survival function, plot the survival curve and estimate the survival time and its 95% CI. The Cochran-Mantel-Haenszel (CMH) method considering the randomization stratification factors is used to perform the hypothesis test for the comparison of response rate between the two groups, and the rate and its 95% CI (Clopper-Pearson method) is estimated for each group. The survival analysis indicators are compared using the stratified log-rank test considering the random stratification factors to compare whether the survival distribution is the same between the two treatments.

**10.3 Analysis plan**

Two data analyses are planned for this study. The first analysis is planned after the last patient completes the study treatment, and the primary analysis parameter is the primary endpoint, ORR. The second analysis is a complete analysis and is performed when a median follow up period of 5 years is reached.

**10.4 Stratified analyses**

The following pre-specified subgroup analyses are planned based on baseline characteristics.

Primary tumor site (left-/right-sided).

Surgical resection of liver metastases (clearly technically unresectable/technically resectable but ≥ 5 metastatic lesions with poor prognosis).

## 11. Adverse events reporting and recording

### 11.1 Definition

Adverse event (AE): The term of adverse event covers the occurrence or worsening of any sign, symptom, syndrome, or disease that occurs in a subject during observation in a clinical study and that affects the health of the subject. This term also includes clinically relevant conditions found in the laboratory or other diagnostic process, such as unplanned diagnosis and treatment; or leading to withdrawal from the trial. An AE may be: a new disease, the worsening of treatment status, symptom or sign, or the worsening of a concomitant disease; the effect of a control drug; a combination of one or more factors unrelated to trial participation. Therefore, the term “AE” does not imply a causal relationship to the investigational drug.

Any untoward medical occurrence that occurs outside of the patient follow-up period specified in this protocol is not an AE.

Some pre-existing conditions, symptoms (such as cancer or other diseases) or medically significant abnormalities confirmed by laboratory tests or instruments (such as ECG) should not be considered as AEs. However, the occurrence of new symptoms as well as the worsening of pre-existing conditions should be considered as AEs. In addition, new abnormalities identified by laboratory or instrumental examination that have a clinical impact on a patient, result in a reduction in the dose of the investigational drug, delay in treatment, or discontinuation of treatment or result in a serious adverse event (SAE) as defined below should be considered as AEs.

SAE: An adverse event that occurs at any dose of the investigational drug or at any time during the observation period, which is as follows:

- 1. Results in death;
  2. Immediately life-threatening, i.e., at the discretion of the investigator, places the patient at risk of death at the time of the event (it does not include an event which hypothetically might have caused death if it is more severe);
  3. Requires inpatient hospitalization or prolongation of existing hospitalization;
  4. Disability refers to an event that can lead to permanent or serious disability/disability of a patient based on clinical determination; disability refers to the significant loss of abilities to carry out activities of daily life;
  5. Results in congenital anomaly (due to the use of medicinal products before fertilization or during pregnancy, resulting the newborn defective;
  6. Medically significant (refers to an event that is not immediately life-threatening or dose not result in death or requires hospitalization, but may jeopardize the patient or may require measures to prevent one of the consequences defined above); requires medical treatment to prevent permanent loss or damage. Examples of such events include: allergic bronchospasm requiring rescue in an emergency room or at home, blood dyscrasias or convulsions that do not require hospitalization.

### 11.2 Scope of expected adverse events

Common adverse reactions:

- Digestive system: diarrhea, nausea, vomiting, abdominal pain, stomatitis, etc. Serious (Grade 3-4) gastrointestinal reactions are relatively rare.
- Blood: neutropenia, anemia, thrombocytopenia.
- Nervous system: headache, paresthesia, vertigo, insomnia, somnolence, etc.
- Skin: rash, exfoliation, etc.
- Others: alopecia, mucositis, pyrexia, weakness, fatigue, hypertension, thrombosis, liver and kidney function damage.

### 11.3 Relevant indicators for determining the causal relationship between adverse events and drugs

Relevant indicators for determining the causal relationship between AEs and drugs: ① Whether there is a reasonable sequential relationship between the time of starting medication and the time of occurrence of suspected adverse reactions. ② Whether the suspected adverse reaction conforms to the known type of adverse reaction of the drug. ③ Whether the suspected adverse reactions can be explained by the patient’s pathological condition, concomitant medication, concurrent therapy and previous therapy. ④ Whether the suspected adverse reactions can be alleviated and resolved after drug discontinuation or dose reduction. ⑤ Whether the same reaction occurs again after re-exposure to the same drug.

Determination of causal relationship between AEs and drug: according to the above five indicators, the causal relationship is determined as the following 5 categories, definite, probable, possible, unlikely and unrelated.

| 1. Definite | The event follows a reasonable temporal sequence from the time of drug administration.  The event resolves after treatment interruption.  AEs been confirmed to reappear after repeated medication (rechallenge). |
| --- | --- |
| 2. Probable | The event follows a reasonable temporal sequence from the time of drug administration.  The event resolves after treatment interruption.  The event cannot be reasonably explained by:  A known symptom of the patient’s clinical condition, or an event caused by other drugs/treatments. |
| 3. Possible | The event follows a reasonable temporal sequence from the time of drug administration.  The event is consistent with the known response to the investigational drug, but the event may also be caused by:  Patient’s clinical condition or other drugs/treatments. |
| 4. Unlikely | The event does not follow a reasonable temporal sequence from the time of drug administration.  The event may have been caused by:  A documented pre-existing condition, or concomitant therapy, or the patient’s clinical condition. |
| 5. Unrelated | The event must have been caused by:  Patient’s clinical condition, or other drugs/treatments. |

### 11.4 Management of adverse events

**11.4.1 Recording of adverse events**

The investigator should explain to the patients and ask them to truthfully reflect the changes in their conditions after medication. Physicians should avoid asking leading questions. Any AEs occurring in the subjects during the trial, including laboratory abnormalities, must be carefully inquired and followed up. All AEs must be determined for its nature, severity and correlation with the drug. The investigator should follow up, observe and record the outcome of all AEs and follow up the patients who withdraw from the trial due to AEs until the AE is resolved. For each event, the following information should be recorded in the AE section of the CRF:

- Severity: Whether an AE is classified as SAE or non-SAE.
- AE: Whenever possible, the specific diagnosis of the event should be recorded. If a diagnosis is not possible, each sign or symptom should be recorded separately, e.g. nausea and vomiting are recorded as two AEs. If an event occurs several times and there is an appropriate time interval to explain that a subsequent condition can be considered a recurring symptom, each AE should be recorded separately on the CRF.
- Start date: The date the event started is recorded. If an abnormal laboratory change is reported as an AE, the date of collection of the first laboratory sample indicating a change in condition is recorded as the start date of the event. The start date of an SAE is defined as the date on which the event begins to meet the criteria for an SAE.
- End date: The date the event ended is recorded. If an abnormal laboratory change is reported as an AE, the collection date of the first post-hoc sample (for which detection can indicate that the condition returns to the pre-event status or returns to normal) is recorded as the end date of the event.
- Relationship to the investigational product
- Therapeutic Intervention: Any therapeutic intervention that is necessary is recorded in the concomitant therapy section of the CRF and noted as drug therapy or non-drug therapy.
- Outcome:

(1) Resolution of the event without sequelae - The patient recovers from the AE without any sequelae observed.

(2) Resolution of the event with sequelae - The patient has recovered from the AE but any sequelae is observed (specify sequelae in the AE section of the CRF).

(3) The event does not resolve - the event persists. (Patients should continue to be followed until definitive final results are available. When follow-up data is collected, follow-up information is recorded in the AE section of the CRF. If the event is serious, a follow-up SAE report needs to be completed.)

(4) Death - The patient dies of an AE. (List the main reason for the patient’s death in the AE section of the CRF, and attach an autopsy report to the CRF, if feasible)

- - Action taken related to the investigational drug:

(1) None - No action is taken related to the investigational drug.

(2) Interruption/adjustment - Withhold the investigational drug and resume when the patient’s symptoms are relieved.

(3) Discontinuation - Permanently discontinue use of the investigational drug.

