**6. Chemotherapy dose adjustment and concomitant medication**

**6.1 Overview**

Toxicities will be assessed according to NCI CTCAE v4.03 criteria starting from the first treatment cycle and will need to be repeated prior to and at the end of each subsequent treatment cycle. The following are general considerations for dose modifications due to chemotherapy-related adverse reactions:

- Dose reductions or interruptions may not be required if, at the discretion of the investigator, the adverse reaction is unlikely to develop into a serious or life-threatening event and will not result in treatment delay or interruption (e.g., alopecia, taste alteration, etc.). If anemia can resolve well with transfusion, no dose reduction or treatment interruption is required.
- If any Grade 1 adverse reactions occur, treatment may be continued at the starting dose without dose interruption.
- Prior to each new treatment cycle, patients should meet the following criteria:

Normal hematologic function (platelets > 90 × 10^9^/L; leukocytes > 3 × 10^9^/L; neutrophils > 1.5 × 10^9^/L).

Serum bilirubin ≤ 1.5 times ULN and transaminases ≤ 5 times ULN.

Serum creatinine < ULN, or calculated creatinine clearance > 50 ml/min (using the Cockcroft-Gault formula).

Recovery to baseline or ≤ Grade 1 from any treatment-related Grade 3/4 non-hematologic adverse reactions (except alopecia).

- If the patient is ineligible for FOLFOXIRI or FOLFOX chemotherapy, treatment with cetuximab or FU/CF chemotherapy can be continued. If the patient is ineligible for cetuximab treatment, FOLFOXIRI or FOLFOX chemotherapy can be continued.

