**6.2 Dose modifications due to hematologic toxicity**

Dose modifications during this or subsequent cycles due to DLT are made as follows:

- For Grade 3 ANC decreased, dose modification of investigational drugs (oxaliplatin/irinotecan, 5-FU) is not needed. For Grade 3 PLT decreased, febrile Grade 3 ANC decreased, or Grade 4 ANC decreased, adjust the dose of oxaliplatin/irinotecan to 80% of the original dose. For Grade 4 PLT decreased or febrile Grade 4 ANC decreased, adjust the dose of oxaliplatin/irinotecan to 70% of the original dose.
- After a dose reduction, if the same or higher grade of toxicity recurs, further reduce the dose of oxaliplatin/irinotecan to 60%. If Grade 4 toxicity persists despite dose modification for Grade 4 toxicity, discontinue oxaliplatin/irinotecan and continue the treatment with cetuximab or FU/CF chemotherapy.
- After the second dose reduction, if the same or higher grade of toxicity recurs, discontinue oxaliplatin/irinotecan and continue the treatment with cetuximab or FU/CF chemotherapy.

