**7.2 Indicators of safety evaluation**

The indicators of safety evaluation of this study include:

- Incidence, severity and serious adverse events of chemotherapy-related adverse events, refer to NCI CTCAE v4.03 criteria;
- Incidence and severity of operation-related complications (perioperative mortality, intraoperative bleeding/transfusion, postoperative blood transfusion and number of blood units used), incidence and severity of systemic complications and local liver complications. Evaluation is completed at 48 hours, 1 month, and 3 months postoperatively using the assessment criteria of Clavien-Dindo grading scale system.

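### The adverse event record labels seriousness as severity and lists no CTCAE grade, although the safety indicator needs the grade

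*Protocol*

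**What the plan says.** The protocol touches on the grading of toxicity in four places.

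- **Section 7.2 (safety indicators):** "Incidence, severity and serious adverse events of chemotherapy-related adverse events, refer to NCI CTCAE v4.03 criteria". Severity and SAEs are named as different things, and CTCAE v4.03 is the reference.
- **Section 6.1 (dose adjustment overview):** "Toxicities will be assessed according to NCI CTCAE v4.03 criteria starting from the first treatment cycle", repeated before and at the end of each later cycle.
- **Section 11.4.1 (recording):** a general sentence, "All AEs must be determined for its nature, severity and correlation with the drug", which names no scale. Then comes the list introduced by "For each event, the following information should be recorded in the AE section of the CRF". Its first item is "Severity: Whether an AE is classified as SAE or non-SAE". The other items are the event term, start date, end date, relationship to the product, therapeutic intervention, outcome and action taken.
- **Section 11.1 (definition):** among the laboratory findings that count as adverse events are "new abnormalities identified by laboratory or instrumental examination that have a clinical impact on a patient, result in a reduction in the dose", or that delay or stop treatment or result in an SAE. Clinically relevant laboratory findings are also included in general terms.

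**The concern.** Seriousness and severity answer different questions. Under Section 11.1 an event is serious because of its outcome or consequence, such as death, immediate threat to life, hospitalization or disability. Severity in Section 7.2 is a CTCAE grade. The recording instruction uses the name of the second for the content of the first, and then lists no place for the second.

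Safety is a secondary objective (Section 2.2), and Section 1 says that triplet chemotherapy carries clearly more toxicity than the doublet, especially hematologic and neurologic. A reader of the results will want Grade 3-4 rates by arm beside the response rates. If sites complete the adverse event record as instructed, that table cannot be drawn from it. A clinical grade that is not written down at the time is hard to reconstruct reliably, and in an open-label trial anyone doing so later may know the arm.

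**Working it through.** No formula applies, so the check sets the sections side by side.

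**1. Does the listed item measure what Section 7.2 needs?** The item has two values, SAE or non-SAE. CTCAE has five grades, and the two scales do not map onto each other. In Appendix III, diarrhea with an increase of seven or more stools per day is Grade 3, and fewer than four is Grade 1. If neither patient is hospitalized and no other SAE criterion is met, both are non-SAE. In the other direction, a lower-grade event that prolongs a hospital stay is an SAE. Section 11.2 blurs the terms again by equating serious gastrointestinal reactions with Grade 3-4.

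**2. Can another listed item stand in for the grade?** The nearest is action taken. Section 6.3 continues the original dose for Grade 1 diarrhea and reduces irinotecan and 5-FU for Grade 2 (to 85%) and Grade 3 (to 75%). The action can therefore separate Grade 1 from higher grades, but Grades 2 and 3 fall into the same action category. It is not a grade.

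**3. Does Section 6.1 supply the missing record?** It requires the assessment each cycle but does not say where the result is entered. The only per-event recording instruction is the list in Section 11.4.1. The dose rules themselves need a grade history: Section 6.2 acts when toxicity of the same or higher grade recurs, and Section 6.5 on a second Grade 3 event.

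**4. Can grades be derived from laboratory data?** Section 9.1 collects hematology and biochemistry on Day 0 and Day 14 of each course, so laboratory grades can be derived for those samples. Diarrhea, stomatitis, neuropathy, hand-foot syndrome and rash cannot be graded from blood results.

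**5. How far does the adverse event definition leave laboratory toxicity out?** Take the neutrophil count.
- Section 6.2 says "For Grade 3 ANC decreased, dose modification of investigational drugs (oxaliplatin/irinotecan, 5-FU) is not needed".
- Appendix III puts Grade 3 below 1.0 and down to 0.5 × 10⁹/L.
- Section 6.1 requires more than 1.5 × 10⁹/L before each new cycle.
- Section 5.2 repeats the regimen every 14 days, so the Day 14 sample falls at the start of the next course.

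Since 1.0 is below 1.5, a Grade 3 count on a scheduled sample before a further course blocks that course. That is a treatment delay, which makes it an adverse event under Section 11.1. What may go unreported is an abnormality with no clinical impact and no dose reduction, delay, discontinuation or SAE. An example is a low count on an unscheduled mid-cycle sample that has recovered by Day 14. Scheduled samples are 14 days apart (14 − 0), so the lowest mid-cycle count may not be sampled at all.

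**The case against.** The strongest reply is that grading is required elsewhere. Section 6.1 demands CTCAE assessment every cycle, Section 9.1 lists chemotherapy-related adverse events at each course, and the dose rules of Section 6 cannot be applied without grades, so investigators must know them. The list in Section 11.4.1 is also only a protocol list: the CRF itself is not shown, and the text directly after the list was not available for this review. The form may well have a grade field.

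Much of this stands. A reader might infer that the graded safety endpoint cannot be produced at all; the documents do not support that. They support only that the written recording rule names the wrong quantity and gives the right one no place. An investigator's knowledge of a grade does not put it in the trial data.

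Four other stronger inferences also fail.

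- **That uncomplicated Grade 3 neutropenia is never an adverse event.** Section 11.1 does not say that laboratory findings count only under the listed conditions. Clinical impact is a separate, judgement-based route, and step 5 shows that a scheduled Grade 3 count before a further course causes a delay.
- **That Grade 1-2 transaminase increases escape because no dose change follows.** Section 6.3 also withholds treatment until recovery to baseline or Grade 1 at most, so a new Grade 2 increase can itself cause a delay.
- **That dose reductions have no category.** The entry that begins "Interruption/adjustment - Withhold the investigational drug and resume when" carries adjustment in its name; only its explanation is narrow.
- **That the undercount can be estimated from the 40% Grade 3/4 agranulocytosis reported in Section 1 for an earlier study of cetuximab plus the triplet.** No document gives the share of such events that would go unreported, so any result would only restate an assumption. Nor is there a matching figure for the doublet arm.

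**Conclusion.** The conflict between Sections 7.2 and 11.4.1 is real. The protocol asks for severity by CTCAE grade and instructs sites to record seriousness under that name, with no grade among the listed items. Followed as written, the adverse event record cannot support a table of Grade 3-4 toxicity by arm, and the loss matters most for clinical toxicities.

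No size can be attached. The documents do not show how many grades would go unrecorded, or whether the loss would differ between arms. The conclusion rests on the list as printed and on the assumption that the CRF follows it; a CRF that already has a grade field would reduce the matter to a wording correction. The laboratory point is secondary and narrow, limited to abnormalities that meet none of the routes in Section 11.1. The primary response-rate analysis is not affected.

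**What to change.** In Section 11.4.1, replace the severity item by two fields: CTCAE v4.03 grade (1-5), and serious (yes/no). Reconcile Sections 6.1, 7.2, 11.1 and 11.4.1, so that the grade assessed each cycle is the grade recorded for each event and the one tabulated.

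As a secondary clarification, state in Section 7.2 or 11.1 that laboratory toxicity is tabulated by worst CTCAE grade per patient from all recorded laboratory values, whether or not it was reported as an adverse event. This covers abnormalities without clinical impact or treatment change. It does not recover low points between the Day 0 and Day 14 samples, and the report should say so.

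The cost is one extra CRF field and a few protocol sentences; the laboratory values are already collected. The downside is slightly more data entry and possibly higher reported toxicity rates. No dose or treatment rule changes.

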## APPENDIX I Karnofsky Performance Status

| **Percent** | **Performance Status** |
| --- | --- |
| 100  90  80  70  60  50  40  30  20  10  0 | Normal no complaints; no evidence of disease  Able to carry on normal activity; minor signs or symptoms of disease  Normal activity with effort; some signs or symptoms of disease  Cares for self; unable to carry on normal activity or to do active work  Requires occasional assistance, but is able to care for most of personal needs  Requires considerable assistance and frequent medical care  Disabled; requires special care and assistance  Severely disabled; hospital admission is indicated although death not imminent  Very sick; hospital admission necessary; active supportive treatment necessary  Moribund; fatal processes progressing rapidly  Deceased |

## APPENDIX II Child-Pugh Classification

| Factor | 1 point | 2 point | 3 point |
| --- | --- | --- | --- |
| Encephalopathy（grade） | None | 1 or 2 | 3 or 4 |
| [Ascites](https://baike.baidu.com/item/%E8%85%B9%E6%B0%B4) | Absent | Slight | Moderate |
| Total bilirubin（umol/L） | <34 | 34－51 | >51 |
| Serum albumin（g/L） | >35 | 28-35 | <28 |
| Prothrombin time（seconds＞control） | <4 | 4-6 | >6 |

Class A：total points（5－6）；Class B：total points（7－9） ；Class C：total points≥10

